**Fig. 2 Fig2:**
[figure not shown]
PACERS logic model

### Control treatment

Control participants will receive usual care which is NERS standard practice: a 16-week structured exercise programme which includes consultations with an exercise professional at the start, 4 weeks, on exiting the scheme (16 weeks) and at 12-month follow-up [6].

### Primary outcome

The primary outcome will be the feasibility and acceptability of the intervention and its proposed evaluation methodology, to inform a decision on whether a full randomised controlled trial is warranted and feasible. This will be assessed against a set of predefined progression criteria related to recruitment and retention rates, exposure to the intervention in both intervention and control groups and acceptability of the intervention, recruitment and randomisation processes to participants. The criteria were agreed by the Trial Steering Committee (TSC) and follow a traffic light assessment system (red = stop; amber = discuss with TSC whether there is enough evidence that sufficient improvements can be made to proceed to full trial without another feasibility assessment; green = proceed) using quantitative measures supported by qualitative data. The criteria, their measurement and assessment criteria are summarised in Table 4. Qualitative data will provide insights into intervention and evaluation design features which need to be retained, or where metrics fall into the amber zone, modifications which may need to be made to improve feasibility and acceptability.

**Table 4 Tab4:** Summary of progression criteria

Progression criteria (PC)	Measures used	Assessment of whether criteria have been met
PC1. Feasibility to recruit a sufficient proportion of new NERS patients to participate in the trial, with appropriate retention rates to 12-month follow-up.	• The percentage of new NERS patients recruited to the trial, and retained at each subsequent follow-up. • Regression models will be used to identify predictors of loss to follow-up (e.g. demographics or baseline motivation).	• If > 20% of new NERS patients recruited = proceed; if < 5% = full-scale trial unlikely to be feasible. If 5–20% the TSC will consider the feasibility of proceeding to a full-scale trial bearing in mind the data and feedback presented and representativeness of the recruited sample, and possible steps to increase the recruitment rate. • If > 80% retained at 12-months = proceed, if < 60% = full-scale trial unlikely to be feasible. If 60–80% the TSC will consider the feasibility of proceeding based on the available data and possible steps to increase retention.
PC2. Intervention and trial methodology delivered as intended	• Summary statistics for intervention fidelity measures overall and by area. • Compliance with study invite processes. • Compliance with randomisation processes.	• The TSC will consider the data presented and make a judgement about whether the intervention and trial methodology were delivered as intended.
PC3. At least one of the two intervention components is acceptable to participants	• Percentages of participants who report acceptability of the intervention components on four self-report questions. • Issues regarding acceptability of, and engagement with, the two intervention components explored in qualitative interviews with a sub-sample of intervention participants.	• The TSC will consider the quantitative and qualitative data and make an overall judgement on whether the intervention is acceptable.
PC4. Recruitment and randomisation processes acceptable to > 50% of recruited participants	• Percentages of participants who report acceptability of the recruitment and randomisation processes on patient questionnaires. • Exploration of understanding and acceptability of recruitment and randomisation processes in qualitative interviews.	• > 50% of recruited participants report ‘agree’ or ‘strongly agree’ to questions about the acceptability of recruitment and randomisation processes. • The TSC will apply discretion in judging whether this criterion has been met, or could be addressed to improve acceptability in a full-scale trial.
PC5. < 20% of control group exposed to the intervention components	• The percentage of participants in intervention and control groups who report that they were provided with a MWK device or accessed the MWC web platform.	• < 20% of control participants report that they have used a MWK device during the study period. • < 20% of control participants report that they have accessed the MWC during the study period.

It is anticipated that in a full trial, the main outcome measure will be objectively measured physical activity using accelerometry. To examine the feasibility of collecting this data at follow-up in the NERS population, a sub-sample of participants will be recruited to complete the accelerometer measure at 16 months post-randomisation. Participants will wear a GT3X ActiGraph accelerometer around the waist for seven consecutive days during waking hours. Data will be processed to identify mean minutes of moderate to vigorous intensity activity per day and mean accelerometer counts per minute (volume of physical activity) using established processes [35].

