### Study objectives

The main objectives for this study are to investigate:the fidelity of delivery of the intervention and trial methodology including compliance with study invitation and randomisation processes;the acceptability of the intervention to participants in terms of its usability and likelihood of future use;whether randomisation is acceptable to 50% or more of participants;the feasibility of recruiting 20% or more new NERS patients and retaining at least 80% of participants at 12-month follow-up (T2);contamination, by exploring whether less than 20% of control participants are exposed to the intervention;the effect of the intervention on the main hypothesised change mechanism (autonomous motivation); andthe feasibility of collecting the primary, secondary and process outcome measures and economic evaluation methods.

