### The intervention

The intervention is an enhanced ERS that includes usual care (NERS standard practice) [6] plus an accelorometry-based activity monitor (MyWellnessKey; MWK). The MWK can be used for self-monitoring of physical activity levels in combination with a linked web platform (MyWellnessCloud) and smartphone application (see Table 2). The MWK has been validated in terms of device accuracy at monitoring physical activity level and intensity [32, 33] and utility at fostering increased physical activity levels (high concurrent validity with ActiGraph accelerometer to detect physical activity in laboratory and free-living environments) [34].

**Table 2 Tab2:** Features of the MWK activity monitor and MyWellnessCloud web platform

• Real-time visual feedback via a screen on the activity monitor	
• Detailed feedback on activity levels via a web platform to indicate progress towards goals, time spent in different activity intensities and calories burned	
• Automatised goal setting via an algorithm which sets goals in a stepwise fashion such that forward progression is mastery-based	
• Facilitation of social support for exercise via the web platform (through involvement in group challenges and remote communication with an exercise professional) and smartphone app (the option to share details about activity completed via social media)	
• Free access to the web platform and smartphone application following discontinuation of use of the MWK via manual input or by linking the account to another monitoring device.	

Intervention participants will be provided with a MWK to use for the remaining 12 weeks of their 16-week NERS programme after receiving it at their 4-week consultation and will be encouraged to use it for 36 weeks after they exit the scheme, up until their 12-month consultation when the device will be returned. In current practice, conducting an 8-month telephone consultation to check clients’ progress with exercise is an optional part of standard care. To encourage participants to maintain engagement in the study, we have asked for the telephone consultation to take place with all intervention participants. Table 3 shows how the intervention will be implemented within the scheme.

**Table 3 Tab3:** Implementation of the intervention components

Time point	Exercise professionals	Intervention participants

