Feasibility of collecting objective data on physical activity at long-term follow-up	ActiGraph accelerometers	The feasibility of obtaining measures of physical activity over a 7 day period.	A linear regression model controlling for age, gender, baseline self-reported physical activity and randomisation group will be fitted. Results will be expressed using regression coefficients, 95% confidence intervals, and standardised effect sizes.	100 participants	16 months post-randomisation
Contamination (PC5)	Self-report questions on study questionnaire on awareness of and exposure to intervention components	Assessment of contamination between trial arms.	Percentages of participants in intervention and control arms reporting exposure to the intervention will be presented alongside 95% confidence intervals.	All participants	T1 and T2

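### PC5 applies the 20% contamination limit to each component separately, so both tests can pass while more than 20% of controls are exposed to at least one component

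*Protocol article*

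**What the plan says.** The limit on contamination appears in four places in the protocol article.

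- **Study objectives:** "contamination, by exploring whether less than 20% of control participants are exposed to the intervention". This is one limit on one group of people.
- **Primary outcome, Table 4, PC5 heading:** "PC5. < 20% of control group exposed to the intervention components".
- **Table 4, PC5, measures used:** the percentage of participants "who report that they were provided with a MWK device or accessed the MWC web platform". The components are joined by 'or'.
- **Table 4, PC5, assessment:** two bullets, "< 20% of control participants report that they have used a MWK device during the study period" and "< 20% of control participants report that they have accessed the MWC during the study period". No bullet covers the two together.

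Table 5 (Process evaluation) adds the planned reporting, from questionnaires at T1 and T2: "Percentages of participants in intervention and control arms reporting exposure to the intervention will be presented alongside 95% confidence intervals". It does not say how the components combine into exposure.

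The Primary outcome section describes a general traffic-light scheme. The PC1 row gives a middle band, and the PC2 to PC4 rows leave the judgement to the Trial Steering Committee (TSC). The PC5 row states neither.

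**The concern.** The objective asks what share of controls met the intervention. The assessment rule answers a different question: whether each component, taken alone, reached fewer than 20% of controls. Two shares that are each below 20% do not keep the share with either one below 20%, unless the same people account for both.

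PC5 is one of five progression criteria that make up the primary outcome. It bears on whether individual randomisation within shared leisure-centre sites can be carried into a full trial. As worded, it can be recorded as met when the study's own contamination objective is not. Because the row has no amber band or discretion of its own, the literal wording carries weight.

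There is also a smaller mismatch. The measure counts controls who were *provided with* a device and the rule counts those who *used* one. A control who was given a device and left it unused counts under the first and not under the second.

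**Working it through.** **Inputs**

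- Total sample 286 (Sample size) and 1:1 allocation (Randomisation), so 286/2 = 143 controls.
- 30% attrition (Sample size), so 143 × 0.7 ≈ 100 controls at 12 months.
- Limit on each component: strictly below 20% (Table 4, PC5).
- Overlap between device use and platform access among controls: not given. It is treated as an assumption and varied from 0% to 100%.

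**The plan's own figures reproduce**

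- Power: an effect size of 0.4 at 80% power and two-sided 5% (two-sided is assumed) needs 99 per arm. Rounded to 100 per arm, 200/0.7 = 286.
- Precision: 1.96 × √(0.25/143) = 0.082, the stated 8.2 points, which is the precision for one arm of 143.

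The sample size is not in question, and 143 is the right denominator before attrition.

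**Largest counts that pass each test**

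- 143 controls: 0.2 × 143 = 28.6, so 28 pass (28/143 = 19.6%).
- 100 controls: 0.2 × 100 = 20, so 19 pass (19.0%).

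**Share exposed to at least one component**

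P(MWK or MWC) = P(MWK) + P(MWC) − P(both). With equal counts k and overlap fraction v (the share of device users who also accessed the platform), this is k(2 − v)/N.

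| Overlap v | 143 controls (k = 28) | 100 controls (k = 19) |
|---|---|---|
| 100% | 28/143 = 19.6% | 19.0% |
| 75% | 35/143 = 24.5% | 23.8% |
| 50% | 42/143 = 29.4% | 28.5% |
| 25% | 49/143 = 34.3% | 33.3% |
| 0% | 56/143 = 39.2% | 38.0% |

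Both tests pass in every row. Only complete or nearly complete overlap keeps the combined share under 20% at these counts. At lower counts the problem shrinks: if each component is below 10%, the combined share cannot reach 20% whatever the overlap.

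**How often the two-part rule passes when true exposure is over the limit** (simulation, 200,000 draws, true rate 15% on each component)

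- 50% overlap, true combined exposure 15% × 1.5 = 22.5%: both tests pass with probability 0.90 (143 controls) or 0.82 (100 controls).
- No overlap, true combined exposure 30%: 0.89 or 0.79.

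**The case against.** The strongest reply is that testing by component was intended. The PC5 heading speaks of components in the plural, PC3 also treats the intervention as two components, and the objective only says that contamination will be explored. On that reading the assessment cell is consistent with its heading. This has some force for the heading taken alone. It does not explain the objective, which refers to the intervention as a whole, or the 'or' in the measures cell.

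The second reply is that overlap should be high, and this largely stands. Table 3 has the exercise professional set up the MWC account and configure the device at the same appointment, and the device is read through that account. Table 2 does describe platform use without the device, but only "following discontinuation of use of the MWK via manual input or by linking the account to another monitoring device", that is, for someone who already had one. A reader might infer from the arithmetic that 35% to 39% of controls would be exposed. Those figures need independence (1 − (1 − 28/143)² = 35.3%) or no overlap at all, and nothing in the protocol supports either.

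A reader might also turn such percentages into a large sample-size penalty for the full trial by assuming that the effect shrinks in proportion to the share exposed. That would credit the full effect of device plus platform to controls who met only one of them, perhaps once. The protocol gives no basis for it.

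Two further complaints might suggest themselves. One is that T1 and T2 reports are not combined, but both rules already refer to the whole study period. The other is that the smartphone application is left out. The questionnaire items are not shown, and use of the application may be counted as MWC access.

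Finally, the TSC sees qualitative data and the Table 5 percentages as well, so a full trial would not be launched on PC5 alone. That limits the harm but does not repair the rule.

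**Conclusion.** The point holds as an inconsistency within a primary-outcome criterion. The objective and the measures cell set one limit on exposure to either component, and the deciding cell does not enforce it. At the largest counts that pass both tests, combined exposure lies between 19.6% and 39.2% with 143 controls, or between 19.0% and 38.0% with 100. It is about 24% to 29% if overlap is between 75% and 50%.

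These figures assume that both components sit just under their limits and that overlap, which the protocol does not give, takes the values shown. Substantial overlap is likely, so the excess is possible rather than expected, and it may be a few points rather than a doubling. The fault does not invalidate the study or its sample size. It is worth correcting because it concerns a decision threshold, the correction costs almost nothing, and it settles the definition of exposure before the results are seen.

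**What to change.** Replace the two assessment bullets in the PC5 row with one test: PC5 is met if fewer than 20% of controls report, at T1 or T2, either use of an MWK or access to the MWC at any time in the study period. Report the two component percentages alongside it, descriptively, with 95% confidence intervals, and use the same definition of exposure in Table 5. Choose either 'provided with' or 'used' and put it in both the measures and assessment cells.

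The cost is one line of Table 4 and one derived variable from responses already planned. The criterion becomes slightly harder to pass: the cap on controls exposed to either component is 28 of 143, where the two-part rule allows up to 56. For example, with a true rate of 15% on each component and 80% overlap (combined 15% × 1.2 = 18%, within the limit), there is a probability of about 0.19 that the single test fails while both separate tests pass.

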### Secondary outcomes

The effect of the intervention on the main hypothesised change mechanism (autonomous motivation) will be evaluated. Other secondary outcome measures will be piloted to estimate key trial parameters (e.g. standard deviation) to inform a future full trial.

#### Measures collected routinely in NERS

Data collected routinely within NERS will be obtained for use within the trial from T0, T1 and T2, as follows:Blood pressure and resting heart rate;Body mass index;Waist circumference;Self-reported physical activity (Scottish Physical Activity Questionnaire) [36];Health-related quality of life (EQ-5D-5L) [37]; andFitness test (Chester fitness test) [38].

#### Measures included in PACERS study questionnaire

The following additional measures will be collected at all time points, which in a full trial would be used to assess effectiveness of the added intervention component (MyWellnessKey):Autonomous Motivation (Behavioural Regulation in Exercise Questionnaire 3 (BREQ-3)) [39];Psychological need support (Intrinsic Motivation Inventory) [40];Anxiety and depression (Hospital Anxiety and Depression Scale (HADS)) [41].

#### Economic evaluation outcome measures

The PACERS study questionnaire will include an adapted Client Service Receipt Inventory (CSRI) based on the previous service use questionnaire used in the NERS evaluation [7] and examples in the DIRUM database (dirum.org) to capture client health and social care service use since the last time point (plus a 4 month retrospective period at baseline). Additional questions in the 12-month questionnaire will capture wider economic outcomes including current work status, days off work due to health problems and estimated income lost due to changes in work during the study period. Willingness to pay for the MWK will also be explored. Baseline demographic data on housing status and household income will also be collected in the PACERS study questionnaire for the purpose of the economic analysis.

### Sample size

The proposed sample size for the study of 286 participants was calculated to allow the estimation of the feasibility proportions of adherence and retention to within at least plus or minus 8.2 percentage points using a 95% confidence interval, as well as to provide 80% power to detect an effect size of 0.4 at the 5% level on the main hypothesised mediator of autonomous motivation at 12-month follow-up, assuming 30% attrition [7]. The sample size was also planned to provide an indication of likely response rates, permit estimates of effect sizes of primary and secondary outcomes in advance of a larger trial and allow exploration of socio-demographic patterning in uptake and use of the MWKs in order to generate hypotheses regarding who the intervention might work for and why.

### Data collection

Routinely collected data will be extracted from the NERS database at all T0, T1 and T2. The PACERS study questionnaire will be mailed to participants at all time points. Telephone and email reminders will be made to non-responders. Semi-structured telephone interviews will be conducted with a sub-sample of intervention participants (*n* = 20) following receipt of the intervention at 4 weeks and again at 12 months (T2) to explore feasibility and acceptability of the intervention and study methods. In addition, telephone interviews will be conducted with a sample of NERS exercise professionals at the same time points to explore feasibility and acceptability of implementing the intervention and study methods from a professional perspective. Figure 3 indicates the schedule of enrolment, interventions and assessments.

**Fig. 3 Fig3:**
[figure not shown]
PACERS study schedule of enrolment, interventions and assessments. *Black-coloured* X indicates study participants and *red-coloured* X indicates intervention delivery staff

### Process evaluation

A detailed process evaluation will examine the acceptability and feasibility of the intervention and evaluation methods, including intervention delivery and fidelity, potential contamination and contextual influences. Quantitative and qualitative data will be collected using a range of methods. Table 5 summarises the process evaluation methods.

**Table 5 Tab5:** Summary of process evaluation methods

Fidelity/feasibility/acceptability	Method of data collection	Aims to explore	Method of analysis/data to be presented	Participants	Time
Fidelity to trial methodology (PC2)	Audio recordings of NERS initial consultations with participants	The accuracy with which recruitment and consent processes were followed.	A summary score of adherence to the processes (range 0–4) will be calculated for each recording and presented overall and by area.	Two participants per exercise professional	T0 (during NERS initial consultation)
Feasibility of implementing the intervention and trial methodology within routine NERS practice	Telephone interviews with NERS staff	Barriers/facilitators, fit with local context, any adverse effects on usual NERS delivery, differences across settings, additional infrastructure or resources required for a full trial.	Thematic analysis.	Two exercise professionals per area	After receipt of the intervention at 4 weeks and at T2
Acceptability of the trial methodology (PC4)	Telephone interviews with NERS staff and intervention participants	Understandings and acceptability of recruitment and randomisation processes.	Thematic analysis.	Two exercise professionals per area, 20 intervention participants	After receipt of the intervention at 4 weeks and at T2
	Self-report questions on study questionnaire		Percentages of participants reporting acceptability of the randomisation process.	All participants	T1
Acceptability of the intervention (PC3)	Telephone interviews with professionals and participants patients	Perceived acceptability of intervention components, barriers and facilitators in using the devices.	Thematic analysis.	Two exercise professionals per area, 20 intervention participants	After receipt of the intervention at 4 weeks and at T2
	Self-report questions on study questionnaire	Frequency of use, ease of use, likelihood of future use.	Percentages of participants reporting that the intervention was easy to use, that they used it, and would do so in the future.	All intervention participants	T1 and T2
Feasibility of collecting objective data on physical activity at long-term follow-up	ActiGraph accelerometers	The feasibility of obtaining measures of physical activity over a 7 day period.	A linear regression model controlling for age, gender, baseline self-reported physical activity and randomisation group will be fitted. Results will be expressed using regression coefficients, 95% confidence intervals, and standardised effect sizes.	100 participants	16 months post-randomisation
Contamination (PC5)	Self-report questions on study questionnaire on awareness of and exposure to intervention components	Assessment of contamination between trial arms.	Percentages of participants in intervention and control arms reporting exposure to the intervention will be presented alongside 95% confidence intervals.	All participants	T1 and T2

